## 2 INTRODUCTION

### 2.1 CURRENT RESEARCH AND STUDY RATIONALE

Stroke is the most common cause of permanent complex disability in adults and one of the most common causes of death worldwide. Around 85% of all strokes are related to acute focal cerebral ischemia (acute ischaemic stroke, AIS) that might be caused by acute occlusion or critical stenosis of one or more intracranial or extracranial arteries (Lindsay MP et al, 2019).

More than 20% of AIS are cardioembolic, most commonly due to atrial fibrillation (AF) (ESC Guidelines, 2016).

Estimates of the Polish Neurological Society (PNS) and the Polish Cardiac Society, as well as preliminary reports from researchers of the NOMED-AF project, suggest that AF (symptomatic and non-symptomatic) affects >23% of the population in the age group > 65 years.

If AF is accompanied by one of the other specific risk factors of AIS, it is an indication for oral anticoagulation (OAC) (CHADS2VASc classification) (Lip GY et al, 2010). The benefit-risk evaluation of OAC administration (reduction of AIS risk vs. increased risk of clinically relevant bleeding) in these patients is clearly positive. However, although OAC therapy (among which the most commonly used are the so-called new OAC [NOAC], i.e., rivaroxaban, dabigatran or apixaban, and rarely others) reduces the risk of AIS by more than 80%, it is still significantly higher than in the general population (1-2% of the annual risk). The incidence of AIS in patients using OAC therapy in Poland has been roughly estimated at 8,000 annually, which includes approximately 5,000 patients on NOAC. Some of these patients might be treated invasively with aspiration and/or mechanical thrombectomy, others (OAC concentration measured by specific test below 50 ng/ml) might be still eligible for thrombolysis, but most of them remain without any approved reperfusion therapeutic possibility as per current clinical management guidelines (PNS Guidelines, 2019).

Recent approvals for NOAC-specific antidotes (idarucizumab, andexanet alfa) provide a therapeutic option for rapid reversal of NOAC anticoagulant effects for serious/life-threatening or uncontrolled bleedings, emergency surgery and/or other urgent procedures (RE-VERSE AD, ANNEXA-4) (Ondexxya SmPC, 2020) (Praxbind SmPC, 2020) (Connolly SJ et al, 2019) (Pollack CV et al, 2017). However, there is poor (dabigatran – idarucizumab) or no (apixaban / rivaroxaban – andexanet alfa) data from clinical trials/studies supporting efficacy and safety of the NOAC-specific antidote + intravenous rtPA sequential therapy.

The aim of this study is to develop and assess the first causative (reperfusion sequential) therapy for this group of patients based on combined anticoagulant reversal and fibrinolytic agents.

Idarucizumab is a humanized monoclonal antibody fragment with structural similarity to thrombin but lacks enzymatic activity. Idarucizumab irreversibly binds to dabigatran (approximately 350-fold stronger than thrombin) with rapid and complete reversal of anti-IIa activity and with no demonstrated pro-coagulation activity. The maximum reversal effect is observed few minutes after antidote administration – approximately 88-98% of anti-IIa activity reduction (Praxbind SmPC, 2020).

Andexanet alfa is a modified recombinant protein analogue of factor Xa. As a result of the removal of the gamma-carboxy-glutamic acid domain (Gla), the protein's ability to attach to the prothrombinase complex has been removed while retaining the native structure and binding factor Xa inhibitors with high affinity (binding and sequestration of the factor Xa inhibitors with minor contribution from the inhibition of tissue factor pathway inhibitor, TFPI). Andexanet alfa is the first approved specific reversal agent for apixaban and rivaroxaban which decreases anti-Xa activity

within two minutes of bolus administration and return to clinically significant levels approximately two hours after end of the infusion (Ondexxya SmPC, 2020).

The STROACT study, a randomized, placebo-controlled clinical trial, will investigate the therapy scheme that includes the two following components administered sequentially:

For the study group A (patients on dabigatran):

- NOAC-specific antidote to reverse the NOAC activity administered intravenously, followed by intravenous thrombolysis with rtPA (bolus and infusion immediately thereafter).

For the study group B (patients on apixaban) and C (patients on rivaroxaban):

- intravenous bolus of NOAC-specific antidote to reverse the NOAC activity, followed by
- intravenous infusion of NOAC-specific antidote initiated parallelly to rtPA bolus administration (if possible) or immediately before the rtPA bolus administration
- intravenous bolus of rtPA (preferably into the contralateral arm or another distant vein) administered parallelly to NOAC-specific antidote infusion initiation (if possible) or immediately after the NOAC-specific antidote infusion initiation
- intravenous infusion of rtPA (initiated immediately after the completion of the rtPA bolus).

The reperfusion treatment with alteplase (rtPA) will be administered intravenously according to the standard protocol at a dose of 0.9 mg/kg of body weight (maximum 90 mg); 10% of the calculated dose in a rapid intravenous injection (bolus) within 1-2 minutes, and 90% of the calculated dose in an intravenous infusion over 1 hour (syringe pump) after exclusion of potential contraindications in accordance with the guidelines of the American Heart Association / American Stroke Association 2018 and 2019, the European Stroke Organization 2019 and experts of the Polish Neurological Society 2019 (PNS Guidelines, 2019) (Actilyse SmPC, 2019).

So far, only a few clinical reports described the effects of administration of idarucizumab in patients with AIS prior to reperfusion therapy with intravenous thrombolysis. No data has been found on the use of andexanet alpha as proposed in this study.

## 2.2 BACKGROUND

The burden of cardiovascular and cerebrovascular diseases has been constantly growing over the last decade and is expected to increase further as the world population ages. There were over 13.7 million new stroke cases in 2016 with estimated 5.5 million deaths (Feigin VL et al, 2019). The age-standardized incidences of stroke were 185 (171.98-198.75) per 100 000 person-years, and 203 (189.24-218.16) per 100 000 person-years after age-adjustment. It is estimated that one in four adults will experience a stroke in their lifetime (Lindsay MP et al, 2019).

The incidence of AIS in Poland is estimated at 70,000 annually.

Ischemic stroke is defined as abrupt onset of neurological deficit related to acute focal cerebral ischemia that might be caused by acute occlusion or critical stenosis of one or more intracranial or extracranial arteries. The acute occlusion of the extracranial or cerebral artery results in substantial tissue hypoperfusion and results in ischemia, and then, potentially, infarction. Final volume of the infarcted brain depends on many factors, mainly on the size and anatomical characteristics of the occluded vessel, severity of cerebral blood flow reduction, time from onset to recanalization, various processes in the brain (brain tissue molecular characteristics), and many other local and systemic factors. The area of the ischemic brain considered as non-salvageable is called the “core”. The hypoperfused tissue immediately surrounding the core is called “penumbra”, which is the main portion of the “tissue at risk” – the potentially salvageable brain after recanalization and reperfusion.

The specific stroke treatment that might lead to recanalization and reperfusion is essential to improve clinical outcome and reduce mortality. The aim of reperfusion therapies in ischemic stroke is to regain functional excellence or independence defined as 0 or 1-2 points on modified Rankin performance scale, respectively. The introduction of two specific therapies for acute brain ischemia – intravenous thrombolysis (IVT) and mechanical thrombectomy (MT), combined with comprehensive, interdisciplinary care provided by stroke units, significantly improved chances for such an outcome (Powers WJ et al, 2019).

Intravenous thrombolysis with recombinant tissue plasminogen activator (rtPA) is the mainstay method of acute ischemic stroke therapy up to 4,5 hours from its onset, with the largest benefits associated with possibly earliest treatment initiation (Emberson J et al, 2014).

More than 20% of AIS are cardioembolic, most commonly due to atrial fibrillation (AF). If AF is accompanied by one of the other specific risk factors of AIS, it is an indication for oral anticoagulation (OAC), or, rarely, in special cases, for low molecular weight (LMWH) or unfractionated heparin (CHADS2VASc classification). The use of oral anticoagulants (OAC) is steadily increasing with the aging society and improving access to medical care (Hindricks G et al, 2020).

The incidence of AIS in patients using OAC therapy in Poland has been roughly estimated at 8,000 annually, which includes approximately 5,000 patients on NOAC. Some of these patients might be treated invasively with aspiration and/or mechanical thrombectomy, others (OAC concentration measured by specific test below 50 ng/ml) might be still eligible for thrombolysis, but most of them remain without any approved reperfusion therapeutic possibility as per current clinical management guidelines (PNS Guidelines, 2019).

The aim of this study is to develop and assess the first causative (reperfusion sequential) therapy for this group of patients based on combined anticoagulant reversal and fibrinolytic agents.

## 2.3 RISK/BENEFIT ASSESSMENT

The STROACT (STROKE on Oral AntiCoagulants for Thrombolysis) is the first ever study to assess the efficacy and safety of sequential reperfusion therapy with the following scheme: non-vitamin K antagonist oral anticoagulant fast-acting specific reversal agent and intravenous thrombolysis therapy with rtPA.

### 2.3.1 KNOWN POTENTIAL RISKS

Patients with AIS are the population with multiple and various comorbidities, and high total cardiovascular risk.

The most severe complication related to rtPA administration is symptomatic intracerebral haemorrhage (sICH), which occurs in 3-7% of all treated patients, and is associated with poor functional outcome (Hacke W et al, 2008) (Sandercock P et al, 2012) (Karaszewski B et al, 2015) (Yaghi S et al., 2014). Meta-analysis of nine trials of rtPA in ischemic stroke (Whiteley WN et al, 2016) showed increased risk of type 2 parenchymal haemorrhage (PH2), of haemorrhage as per SITS-MOST definition, and fatal intracerebral haemorrhage in IVT group.

In REVERSE-AD trial (A Study of the RE-VERSAl Effects of Idarucizumab on Active Dabigatran), a multicentre, prospective, open-label study, patients with life-threatening or uncontrolled bleeding and patients who required emergency surgery or other urgent procedures, were treated with 5.0 g of intravenous idarucizumab. Median maximum reversal value was 100% in the first 4 hrs. Most patients achieved complete reversal as measured by ECT (82%), or dTT (99%). The adverse reactions reported in ≥5% of patients were constipation and nausea. In 33 (6.56%) patients reported thrombotic

events, and most of these patients were not on antithrombotic therapy at the time of the event (Pollack CV et al, 2017).

In ANNEXA-4 trial (The Andexanet Alfa, a Novel Antidote to the Anticoagulation Effects of Factor Xa Inhibitors), a single-group cohort study, patients with acute major bleeding – 64% intracranial and 26% gastrointestinal – were treated with andexanet alfa in intravenous bolus over 30 minutes, followed by continuous infusion for 120 min. Median anti-FXa activity decreased was 92% for both apixaban and rivaroxaban patients. There were 34 patients (10%) with a thrombotic event during 30-day follow-up period (Connolly SJ et al, 2019).

---

### 2.3.2 KNOWN POTENTIAL BENEFITS

Specific AIS treatment therapies – intravenous thrombolysis (IVT) and mechanical thrombectomy (MT), combined with comprehensive, interdisciplinary care provided by stroke units significantly improve chances for excellent and good functional outcomes (mRS 0-1 and 0-2, respectively).

Reversing NOAC activity with administration of fast-acting specific reversal agents (antidotes): idarucizumab for dabigatran, and andexanet alfa for apixaban or rivaroxaban, has been shown to be an effective and safe emergency treatment for major, life-threatening bleeding complications of NOAC therapy, or as a prevention of bleeding in patients requiring emergency surgery, or invasive procedures (Ondexxya SmPC, 2020) (Praxbind SmPC, 2020).

Taking that maximum reversal effect of idarucizumab is observed within few minutes from bolus administration, and high proportion of patients show complete neutralization of anticoagulant activity (Ondexxya SmPC, 2020) (Praxbind SmPC, 2020). it is possible that the sequential reperfusion intravenous therapy with rtPA soon after idarucizumab might result in outcomes similar to those observed in large rtPA stroke trials.

Similar benefits might be expected from reversing anti-Xa activities by andexanet alfa followed by administration of intravenous rtPA. However, there is no single empiric data of this therapeutic approach, and the mechanisms of action with all pharmacodynamic and pharmacokinetic characteristics, and potential harms related to not only bleeding, but also thromboembolic complications as assumed from complex pathophysiological relations, are different for andexanet alfa in comparison to idarucizumab.

---

### 2.3.3 ASSESSMENT OF POTENTIAL RISKS AND BENEFITS

The STROACT is the first ever study to assess the efficacy and safety of sequential reperfusion therapy with the following scheme: non-vitamin K antagonist oral anticoagulant fast-acting specific reversal agent and intravenous thrombolysis therapy with rtPA.

There is an urgent clinical need to develop and assess the first causative (reperfusion) therapy for ischemic stroke patients on NOAC with anti-IIa/anti-Xa activity > 50 ng/ml or respective blood concentration of dabigatran. To minimize all peri-procedural risks and maximize patients' safety, we developed detailed and clear inclusion and exclusion criteria in accordance with EBM. The main safety endpoint is the rate of symptomatic intracranial haemorrhages (sICH). To follow-up these, in the management protocol we incorporated two neuroimaging testing (scanning) during the first week after randomisation: the first CT/MRI is going to be performed at 24 hours  $\pm$  4 hours after rtPA bolus, and MRI - 7 days  $\pm$  1 day (24 hours) from rtPA bolus.

All hospitals participating in the STROACT study are comprehensive stroke centres (CSC) with extensive experience in specific acute ischemic stroke treatments.

Incoming clinical safety data will be monitored and reviewed by IDMC to reassure patients' safety and scientific integrity of the study.

### 3 AIMS, OBJECTIVES AND ENDPOINTS

This study aims to evaluate the efficacy and safety of the reperfusion thrombolytic therapy with rtPA in patients with acute ischaemic stroke (AIS) on non-vitamin K antagonist oral anticoagulants (NOAC), after neutralisation of the NOAC anticoagulant activity (administration of a specific antidote) who do not qualify for mechanical thrombectomy.

#### 3.1 PRIMARY OBJECTIVE

| Objective                                                                                                                                                                                                | Outcome measure / Endpoint                                                                                                                                                                                |
|----------------------------------------------------------------------------------------------------------------------------------------------------------------------------------------------------------|-----------------------------------------------------------------------------------------------------------------------------------------------------------------------------------------------------------|
| Efficacy                                                                                                                                                                                          |                                                                                                                                                                                                           |
| To assess the efficacy of the investigational therapy in patients with acute ischaemic stroke on the non-vitamin K antagonist oral anticoagulants compared to placebo using modified Rankin Scale (mRS). | Proportion of patients with excellent and good functional outcome assessed with modified Rankin scale (mRS) (mRS 0-1 and 0-2, respectively) at 90 days (+/- 3 days) after study treatment administration. |

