## 5 STUDY POPULATION

Previously functionally independent patients (0-2 points on the modified Rankin scale) taking one of the oral non-vitamin K antagonist oral anticoagulants (rivaroxaban, apixaban or dabigatran) as a prevention of cardioembolic and/or thromboembolic events, who despite maintaining adequate therapeutic anti-IIa/anti-Xa activity, which is directly proportional to the plasma NOAC concentration, have an ischemic stroke in the absence of another possibility of AIS specific treatment (i.e. primary mechanical thrombectomy treatment cannot be used – no occlusion of large cerebral/intracranial artery).

Detailed inclusion and exclusion criteria are provided in [Section 5.1](#) and 0 respectively. Patients who do not meet the eligibility criteria requirements for the STROACT study are described as screen failures; refer to [Section 5.4](#).

Prospective approval of protocol deviations to recruitment and enrolment criteria, also known as protocol waivers or exemptions, is not permitted.

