## 6.4 RANDOMISATION

Subjects allocated to A, B, or C study group (arm), defined by NOAC taken before AIS onset (see [Section 4.1](#)), will be randomized in 1:1 ratio to receive either active treatment or placebo (comparator).

A stratified variable block length randomization based on a computer-generated randomization schedule integrated into the eCRF software will be used (see [Section 7.3.1](#)).

Stratification will consider severity of the IS at randomization (<6 points in NIHSS, and ≥6 points in NIHSS).

---

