### 11.2 STATISTICAL HYPOTHESES

The null hypothesis assumes that proportion of subjects randomized to study treatment achieving a primary endpoint (p) is lower than proportion in placebo group (p0):

$$H_0: p - p_0 \leq \delta$$

$$H_a: p - p_0 > \delta,$$

where  $\delta$  is a non-inferiority margin (-15%).

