### 11.3 SAMPLE SIZE DETERMINATION AND PLANNED RECRUITMENT RATES

Due to nature of this study (proof of concept phase II trial), with effect size being unknown, following assumptions were made:

- Proportion of subjects randomized to receive IMP achieving primary endpoint will be 40% and this proportion will be identical in a placebo group
  - A non-inferiority margin  $\delta$  will be equal to 15%
  - One sided significance level 0.2
  - Power of 70%
  - One interim analysis (with Hwang-Shih-DeCani  $\alpha$  pending function)
  - A drop-out rate of 10%.
- Taking these into consideration, a minimal number of subjects per group is 46 – so 92 subjects in each study arm.

Sample size calculations were made in R version 3.6 using gsDesign library version 3.1.1.

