### 11.5.2.1 ANALYSIS OF THE PRIMARY ENDPOINT

Primary endpoint analysis for each study arm (dabigatran, apixaban, or rivaroxaban) will be performed independently. Proportion of subjects achieving primary endpoint for active treatment and placebo as well as difference of proportions together with 82% Confidence Interval (CI) will be calculated. One-sided noninferiority test with 15% margin for difference in proportions will be performed. A p value lower than 0.176 will be considered as statistically significant.

---

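### The primary endpoint names two nested cut-offs, mRS 0-1 and mRS 0-2, but the plan sizes and tests one proportion and gives no rule for choosing or combining them

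*Protocol*

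**What the plan says.** Protocol sections 1.1.3.1 and 3.1 give the primary outcome as "Proportion of patients with excellent and good functional outcome assessed with modified Rankin scale (mRS) (mRS 0-1 and 0-2, respectively") at 90 days. Section 4.3 repeats both cut-offs and selects the mRS as primary outcome without choosing between them.

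The statistical sections speak of one endpoint:

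- Section 11.2 has one proportion p, one p0 and one margin of 15 points.
- Sections 1.1.9.1 and 11.3 assume "Proportion of subjects randomized to receive IMP achieving primary endpoint will be 40% and this proportion will be identical in a placebo group", with "One sided significance level 0.2", 70% power and 10% drop-out, giving 46 per group.
- Section 11.5.2.1 reports the "Proportion of subjects achieving primary endpoint for active treatment and placebo" and applies one non-inferiority test at p<0.176 in each arm.
- Section 11.5.4.1 applies one interim test at one-sided 0.0238.

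Section 1.1.9.1 rules out any multiplicity correction beyond the interim. Its stated reason is that arms are not compared with each other; it does not mention the two cut-offs.

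Section 5 admits "Previously functionally independent patients (0-2 points on the modified Rankin scale"). Section 3.2 restricts the secondary mRS 0-1 endpoint to patients with pre-stroke mRS 0-1.

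**The concern.** With two cut-offs and one undefined success criterion, the same data could be declared positive or negative depending on a choice made later. If success on either cut-off counts, there are two chances to pass at a level meant for one. If both must succeed, power falls below that of a single test. The alpha of 0.20 and power of 70% are already lenient, so there is little room for either.

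The single 40% is a sign that only one endpoint was sized. Because mRS 0-1 is contained in mRS 0-2, both rates can be 40% only if no patient scores exactly 2.

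The choice of cut-off also matters for patients who enter with pre-stroke mRS 2. They can hardly reach mRS 0-1, so they would tend to count as failures in both groups and pull that difference towards zero. That favours non-inferiority.

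**Working it through.** **Inputs from the protocol.** Rate 40% in both groups, margin 15 points, one-sided alpha 0.20, power 70%, drop-out 10% (11.3); 1:1 allocation (6.4); interim level 0.0238 (11.5.4.1); final threshold 0.176 (11.5.2.1). The per-protocol set, which is the main efficacy set, requires a day-90 mRS (11.4.2), so 46 × 0.9 = 41 evaluable per group.

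**Assumption.** The protocol gives no separate rate for each cut-off. I use pairs (mRS 0-1 / mRS 0-2) from 25/40% to 40/60%.

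**Step 1: the plan's own figure.** For one endpoint,

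n = (z₀.₈₀ + z₀.₇₀)² × 2p(1−p) / 0.15² = (0.842 + 0.524)² × 0.48 / 0.0225 = 39.8, so 40 per group.

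Drop-out: 40 / 0.9 = 44.4, so 45. Adding a Hwang-Shih-DeCani interim at half the information (gamma = −4 assumed, which reproduces 0.0238) gives 44.5 to 47.0, depending on the futility option. The stated 46 is therefore right for one 40% endpoint.

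**Step 2: sensitivity to the rate.** At 41 evaluable and alpha 0.20, power = Φ(0.15 / √(2p(1−p)/41) − 0.842). At 40% this is Φ(1.386 − 0.842) = 0.71; over rates of 30 to 60% it is 0.70 to 0.74. The shared 40% hardly affects power, so the missing rule is what matters.

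**Step 3: correlation of the two tests.** For nested indicators, the covariance within a group is p₁(1−p₂). With 40/50% in both groups, the correlation is 2 × 0.4 × 0.5 / √(0.48 × 0.50) = 0.82. Over the assumed pairs it is about 0.65 to 0.90.

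**Step 4: operating characteristics.** Simulation of mRS 0-1 / 2 / 3-6, 41 per group, unpooled Wald test on each cut-off. Error is with both true differences at −15 points; power is with equal groups.

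| Rates 0-1 / 0-2 | Single-test error | Either passes: error | Single-test power | Both must pass: power |
|---|---|---|---|---|
| 25/40 | 0.19, 0.19 | 0.28 | 0.74, 0.69 | 0.61 |
| 30/40 | 0.18, 0.19 | 0.26 | 0.73, 0.69 | 0.62 |
| 35/50 | 0.18, 0.18 | 0.26 | 0.71, 0.64 | 0.57 |
| 40/50 | 0.19, 0.18 | 0.25 | 0.69, 0.65 | 0.58 |
| 40/55 | 0.19, 0.16 | 0.25 | 0.69, 0.66 | 0.57 |
| 40/60 | 0.19, 0.16 | 0.26 | 0.69, 0.69 | 0.57 |

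The table is at p<0.176. A normal approximation puts the lowest both-must-pass power at 56%. With cut-offs only 5 points apart (40/45) the figures are 0.24 and 61%. At nominal 0.20 the tabled pairs give about 0.27 to 0.30 and 60 to 64%. With the interim boundary included (0.0238, then 0.176), the error is 0.23 to 0.27 against 0.18 for one test, and both-must-pass power is 56 to 61%.

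**Step 5: what each rule would need.**

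- Both must pass at alpha 0.20 and 70% power: 51 to 59 evaluable, about 57 to 66 per group after drop-out (mRS 0-1 at 30 to 40%, mRS 0-2 at 40 to 60%).
- Bonferroni at 0.10 each: (1.282 + 0.524)² × 0.48 / 0.0225 = 69.6, so 70 evaluable and 70 / 0.9 = 78 per group, for 70% power on one 40% endpoint.
- One cut-off as sole primary, or first in a fixed sequence: 46 per group and alpha 0.20 stand.

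**The case against.** A reader might infer that the trial's type I error is inflated, or that it is underpowered. The documents do not support either as a fact. The protocol adopts neither an either-passes nor a both-must-pass rule, and if one cut-off is the sole or first-tested primary, both stated figures stand.

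There is also a single-endpoint reading. The endpoint is worded as one proportion, and section 2.2 describes the treatment aim as mRS 0 or mRS 1-2, whose union is mRS 0-2. On that reading the 40% belongs to mRS 0-2. It remains uncertain, because sections 3.1 and 4.3 pair the two outcome labels explicitly with 0-1 and 0-2.

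Not all of the shortfall from 70% comes from the second cut-off. At p<0.176 a single 40% endpoint with 41 evaluable has only about 69% power, so the single-test column is the fair comparator. Section 1.1.9 also expects about 100 per arm; at 45 evaluable per group, both-must-pass power is about 60 to 63%.

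The pre-stroke mRS 2 argument cannot be sized from the documents. If such patients never reached mRS 0-1 and made up an assumed 10 to 30%, a 15-point deficit in the others would shrink to 15 × 0.9 = 13.5 or 15 × 0.7 = 10.5 points, but their share is unknown. Section 3.2 gives no reason for its restriction, so it does not show that the sponsor had this dilution in mind.

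A SAP could supply the rule. That does not remove the mismatch within the protocol. Sections 1.1.10 and 11.1.2 require the SAP only before final database lock, and the efficacy interim comes earlier.

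**Conclusion.** The point holds as a specification fault: two nested cut-offs are named as primary, one is sized and tested, and nothing says which one or how two would be combined. Alpha 0.20 and power 70% hold together only if one cut-off is the sole or first-tested primary, which the protocol does not state.

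The error and power figures are scenarios. They depend on a rule the protocol has not chosen, on assumed rates for each cut-off, and on 41 evaluable per group. What is certain from the text is that the success criterion is open in each of the three arms, at both the interim and the final analysis.

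**What to change.** Before the unblinded interim:

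- Name one cut-off as the sole primary, or fix a testing order, and make the other secondary or second in sequence.
- State which cut-off the 40% belongs to.
- Align sections 1.1.3.1, 1.1.9.1, 3.1, 4.3, 11.2, 11.3, 11.5.2.1 and 11.5.4.

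mRS 0-2 is a natural choice, because it is open to everyone eligible, including patients with pre-stroke mRS 2, and mRS 0-1 already has a secondary endpoint. The choice is the sponsor's; 46 per group stands with either cut-off.

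The cost is an amendment to the wording. The full mRS is already recorded at day 90, so data collection does not change. Keeping both cut-offs as required, or splitting alpha, would cost patients as shown in step 5 of the working.
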